## Abstract

**Background:**

Literature shows a high prevalence of psychological distress (PD) as well as common mental disorders (CMD) such as major depressive disorders (MDD), generalized anxiety disorders (GAD), post-traumatic stress disorders (PTSD), and substance misuse disorders (SUD) among people exposed to disasters and pandemics like the COVID-19. Moreover, CMD are associated with increased mortality (mainly through suicide) and morbidity (loss of productivity). A number of countries have made deliberate efforts to identify and manage CMD in light of COVID-19. However, low levels of mental health literacy (MHL) manifested by the individual’s unawareness of CMD symptoms, limited human and mental health infrastructure resources, and high levels of mental illness stigma (MIS) are barriers to integration of mental health care in general health care during pandemics and epidemics such as the COVID-19.

**Objectives:**

For the proposed study, we will determine effectiveness of a psycho-education intervention delivered by village health team (VHT) members.

**Methods:**

We will employ a cluster randomized trial design in 24 villages in central Uganda. We will collect baseline data to and document the prevalence of MHL, PD, MDD, PTSD, GAD, and SUD. We will distribute information education and communication materials (IEC) aimed at improving MHL to 420 adult individuals in the intervention arm (*n* = 12 villages). In the control arm (*n* = 12 villages), VHTs will distribute ministry of health COVID-19 information leaflets to 420 participants. Within 7 days of distributing the materials, research assistants will conduct a follow-up interview and assess for the same parameters (MHL, PD, MDD, PTSD, GAD, and SUD). We will use an intention to treat analysis to estimate the effectiveness of the psycho-education intervention.

**Discussion:**

Findings from this research will guide policy and practice regarding the integration of mental health services in the community in the context of epidemic preparedness and response.

**Trial registration:**

ClinicalTrials.govNCT04616989. Registered on 05 November 2020

## Background

During disasters and pandemics such as the COVID-19, up to 10% of individuals in the community may suffer from moderate to severe psychological distress (PD) [1–3]. In the majority of individuals, PD is transient and abates by itself [4]. However, in some individuals, severe PD resulting from exposure to disasters may trigger the onset of common mental disorders (CMD) such as major depressive disorders (MDD), generalized anxiety disorders (GAD), post-traumatic stress disorders (PTSD), and substance misuse disorders (SUD) [5–7].

Moreover, literature shows that CMD predicts poor outcomes including high mortality (mainly through suicide) [8–10] and morbidity (low productivity and poor quality of life) [11, 12]. Due to the high prevalence of CMD among individuals exposed to disasters and the adverse events that result from it, a number of scholars have recommended that CMD are identified and adequately treated using psychological or pharmacological therapies [13–16]. However, despite the huge burden and negative consequences, CMD are rarely identified and inadequately treated in low resourced sub-Saharan Africa (SSA). A number of barriers may be responsible for the poor identification of CMDs.

First, there is a severe shortage of specialized mental health care workers in SSA—with just a psychiatrist per million persons in low resourced settings compared to 1 per 10,000 persons in high income countries [17, 18]. Lack of specialized mental health care workers continue to be a barrier to the delivery of mental health care in both specialized and primary care settings. Second, high levels of mental illness stigma (MIS) [19, 20] as well as poor mental health literacy (MHL) [21–23] that have been reported in SSA continue to hinder delivery of mental health care. Jorm (1997) [24] defines MHL as the ability to recognize the signs and symptoms of mental illnesses, know their causes, and identify sources of help (both lay and professional). The low level of MHL and high MIS are significant barriers to accessing care especially in light of the COVID-19 where there has been severe disruptions in movement of people to access care—in SSA settings, mental health care is mainly delivered at health facilities [25, 26]. Novel means of improving MHL and reducing MIS in light of the COVID-19 pandemic are urgently needed.

One of the interventions that can help enhance knowledge about mental health is psycho-education. The American Psychiatry Association [27] defines psycho-education as improvement in the knowledge in the subject areas that serve the goals of treatment and rehabilitation. However, findings about the efficacy of psycho-education are conflicting. Whereas some studies show that psycho-education as adjunct therapy leads better outcomes including better self-efficacy [28, 29], others studies have not documented benefits related to psycho-education [30–32]. Moreover, low levels of literacy [33–35] in SSA means that psycho-education interventions may be difficult to deliver. Novel means of delivering psycho-education materials in SSA are urgently needed.

For the proposed study, we will document baseline prevalence of MHL and CMD. To the best of our knowledge, this will be among the very first studies to examine the effectiveness of a psycho-education intervention in a community setting in the context of the COVID-19 pandemic.

### Objective

For the proposed study, we will determine effectiveness of a psycho-education intervention delivered by village health team (VHT) members.

### Study outcomes

Our primary outcome will be a mean change in MHL between the two arms. The secondary outcome will be associations between the MHL and demographic and CMD variables assessed by way of regression analysis.

## Methods

### Study design and setting

For the proposed study, we will use an open-label cluster-randomized trial of 24 randomly chosen villages (*n* = 12 intervention and *n* = 12 control) in Kampala (*n* = 15), Wakiso (*n* = 3), Mukono (*n* = 4), and Masaka (*n* = 2) districts. Intervention and control villages are located at least 20 km apart to avoid contamination

### Eligibility criteria

Individuals will be eligible for recruitment if they have been residing in the selected villages for a minimum of 6 months and do not intend to migrate or move/shift residence in the next month after being approached. Individuals will be eligible for recruitment if they are at least 18 years of age. All participants will be required to provide written informed consent. For those who can neither write nor read, the consent form will be read to them by trained research assistants (RA) and they will use a thumb print soaked in an inkpad to provide informed consent. The RA will be graduate level social scientists with experience in data collection.

### Study procedure

(i) Development of materials. We will engage with the mental health department at the ministry of health of Uganda to develop information and education communication (IEC) material—the aim of the IEC materials is to address the key barriers to mental health care access (low MHL and high MIS). The VHTs will distribute the IEC materials (described in the methods section) in the intervention villages. In the control villages, VHTs will distribute the ministry of health of Uganda leaflets that contain the COVID-19 prevention strategies.

(ii) Randomization and sampling: We shall send a list of all the villages in the districts (5250) to our statistician ([name]). We will then employ the multistage sampling approach to select 840 participants from 24 randomly selected villages located in the 362 parishes (5250 villages) that span the study districts. These villages will then be provided to the PI who will contact the VHTs in the said villages. Study villages will be selected using the probability proportional to size approach (based on number of parishes/villages per district). Thus, we shall select 15 villages from Kampala district (3297 villages), 4 villages from Mukono district (813 villages), 2 villages from Masaka district (436 villages), and 3 villages from Wakiso district (704 villages). The villages are at least 20 km apart to minimize contamination between the study arms (individuals interacting with each other during the intervention).

(iv) Baseline data collection: At baseline, trained research assistants will collect demographic (age, gender, education level and place of residence) information and administer the Mental health Knowledge Schedule (MAKS) [36] to assess for MHL, Kesler-10 (K-10) [37] to measure PD, the Generalized Anxiety Disorder scale (GAD-7) [38] to assess for GAD, Patient Health Questionnaire-9 (PHQ-9) [39] to assess for MDD, Post-Traumatic Stress Disorder-Primary Care Screen (PTSD-PC) [40] for PTSD, and the Alcohol Smoking and Substance Involvement screening Test (ASSIST) [41] to assess for SUD. This data will be collected from participants in both arms. During the baseline data collection, the IEC materials will be distributed to participants in the intervention arm and the ministry of health (MOH) brochures to participants in the control arm.

(v) The intervention: VHTs will distribute the IEC materials to the 12 intervention villages described above after collection of baseline data and encourage participants to read these materials. In the 12 control villages, VHTs will distribute the MOH brochures that contain information about (a) the signs and symptoms of the COVID-19 and the preventive measures, (b) the fact that individuals may suffer from stress during the pandemic, (c) the sources from where they can get psychosocial help, and (d) the contact details of the research team should they need more information. The information contained in the ministry of health brochures are the current standard of care for community members. The IEC materials will be distributed to individuals who participated in the baseline surveys.

(vi) Mitigating the possibility of contamination between the study arms: Being an educational intervention, it is not possible to blind the participants in the control villages from receiving information meant for those in the intervention arm. Thus, there is a chance that participants in the control villages will access IEC materials distributed to those in the intervention arm, leading to contamination of our findings. To avoid contamination, we will do the following: (i) randomize villages so that they are at least 20 km apart (with the limited human movements during the COVID-19 pandemic, we anticipate that there will be little by way of people sharing the IEC materials), (ii) conduct the assessments within a week of distributing the materials to limit the chances that the information will be widely circulated, and (iii) ask participants in the control arms if they accessed the IEC materials meant for the control group—we will document the number of individuals who fall in this category. We have no control of other educational interventions that may be instituted during the trial period and circulated using the mass media. However, these interventions are usually sanctioned by the MOH—we are already working with the MOH and will know the nature and extent of these interventions if any. In the event that individuals are provided with similar information, then we will find out how many of them received it and acted on them. However, the trial period is quite short (7–10 days) and we believe that we can engage the MOH to implement these interventions after our intervention is complete.

(vii) Follow-up data collection: The same trained RA’s will collect follow-up data within a week after the VHTs have distributed IEC materials. The RA’s will administer the instruments administered at baseline (MAKS, K-10, GAD-7, PHQ-9, PTSD-PC, and ASSIST). The RA’s who collected the baseline data will be the same ones to collect the follow-up data. They would have set up appointments for the follow-up interview and will know the terrain well enough. The time duration between baseline and follow-up is a week. However, in some situations where the participant cannot be accessed within the week, we will give an allowance of up to 4 weeks within which to conduct the follow-up interviews—should the participant not be available within the said 4 weeks, then we will consider them as lost to follow-up.

(viii) Access to services. The leaflets distributed to participants from both arms will contain our study team phone numbers; participants can call and get help if need be. We will request that individuals without phones or those who may not have the money to call contact their VHTs (who are residents of the village) and request to make the calls using the VHT’s telephone. Research assistants will then assess the participants from CMD, and make appropriate decisions including referral to the nearest MOH psychosocial team members.

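### The plan's only stated measure of cross-arm contamination asks controls about materials meant for the control group, probably a slip for the intervention group

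*Protocol article*

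**What the plan says.** Item (vi) of Study procedure (protocol article) accepts that an educational intervention cannot be masked from control villages, and states the risk as the chance that "participants in the control villages will access IEC materials distributed to those in the intervention arm".

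It then lists three safeguards:

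- villages at least 20 km apart;
- assessment within a week of distribution;
- a question to controls, under which staff will "ask participants in the control arms if they accessed the IEC materials meant for the control group", followed by the commitment that "we will document the number of individuals who fall in this category".

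Which arm gets which material is stated several times. Item (iv) says "IEC materials will be distributed to participants in the intervention arm and the ministry of health (MOH) brochures to participants in the control arm". Item (i) says "In the control villages, VHTs will distribute the ministry of health of Uganda leaflets that contain the COVID-19 prevention strategies". Item (v) again assigns MOH brochures to the 12 control villages. The abstract gives the planned number: "VHTs will distribute ministry of health COVID-19 information leaflets to 420 participants".

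Item (vi) contains one more exposure check: "In the event that individuals are provided with similar information, then we will find out how many of them received it and acted on them". It follows a sentence on other educational interventions circulated through the mass media.

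**The concern.** The question in the third safeguard does not match the exposure that the paragraph sets out to detect. Contamination here means a control participant seeing the intervention leaflet. The question names material belonging to the control group.

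This is an instruction on what to ask and what to count, not background text, and it is the only place where the article says how cross-arm exposure will be measured. The trial is open-label, its intervention is a printed item that can be passed on, and the plan itself concedes that contamination may happen. Follow-up may also run to 4 weeks for participants who cannot be reached within the week, which weakens the second safeguard for them.

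At stake is how the result can be read. If the arms differ little, the investigators will want to know whether the leaflet did not work or whether controls also had it. A count of the wrong exposure cannot help with that.

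**Working it through.** The article states no figure for contamination, so there is nothing to reproduce. The check compares the relevant statements.

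| Question | Where in the protocol article | Answer |
|---|---|---|
| What is contamination? | Study procedure (vi), opening | Controls obtaining the intervention arm's IEC materials |
| Who receives IEC materials? | Study procedure (iv); also (i) and the abstract | The intervention arm |
| Who receives MOH leaflets or brochures? | Study procedure (i), (iv), (v); abstract | The control arm, 420 planned |
| What are controls asked? | Study procedure (vi), third safeguard | Whether they accessed IEC materials meant for the control group |
| What is recorded? | Study procedure (vi), third safeguard | The number who say they did |

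**Step 1.** The exposure in the first row and the question in the fourth row are different. The sentence contradicts its own paragraph.

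**Step 2.** The phrase can be read in two ways.

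- *Stress on the group named.* The only material meant for controls is the MOH leaflet. The count then records delivery of that leaflet. If distribution goes as planned, it approaches 420 of 420 whether the number who saw the intervention leaflet is zero or large.
- *Stress on the term IEC materials.* In the passages that allocate materials, this term denotes the intervention materials. The control group then has no IEC materials, and the phrase describes nothing that exists. What a participant would understand by it cannot be predicted.

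Neither reading, taken literally, gives a count of contaminated controls.

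**Step 3.** Does anything else in the article repair it?

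- The first two safeguards are preventive and measure nothing.
- The check on similar information concerns outside campaigns, not the other arm's leaflet.
- The follow-up instruments listed in item (vii) (MAKS, K-10, GAD-7, PHQ-9, PTSD-PC, ASSIST) cover literacy, distress, mental disorders and substance use. None is named as an exposure question.
- No other section states the question correctly.

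**Step 4.** Does the count enter the main analysis? Under Statistical analysis, Objective 2, MHL is compared between arms by intention to treat. The contamination count is not used there, so an error in it cannot change that estimate.

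**The case against.** The strongest reply is that this is a drafting slip whose intended meaning is plain. The heading of item (vi) is contamination between arms, the risk is described correctly shortly before the list, and the question is offered as a safeguard against that risk. The article also describes the question without reproducing it. Participants would hardly be asked about control-group materials in those words, and the questionnaire, which is not shown, may be correct. Most of this stands. It makes the harm conditional on the wording reaching the field, and it limits the weight of the point. It does not remove the contradiction. The MOH brochure also mentions stress and sources of psychosocial help, so a loosely worded item could draw yes answers about the wrong leaflet.

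A reader might infer three stronger claims that the documents do not support.

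- *The count will be 420 of 420.* That is one of two readings of a self-contradictory phrase, and it assumes complete delivery.
- *The trial loses serious power.* Dilution would come from contamination itself, and correcting the word restores no power. Nor do the plan's inputs place the trial at 80% power. Under Sample size and statistical considerations they are a mean of 14.14, a 50% increase (to 21.21, difference 7.07), SD 2.19, 35 per village and a coefficient of variation of 0.25. The standard formula for cluster means gives 1 + (1.96 + 0.84)² × [2 × 2.19²/35 + 0.25² × (14.14² + 21.21²)] / 7.07² = 1 + 7.85 × 40.89/49.98 = 7.4. This rounds up to the plan's figure of about 8 villages per arm. With the 12 planned, the noncentrality is 7.07/√(40.89/12) = 3.83, and power with 22 degrees of freedom is about 96%. If 10% or 20% of controls were fully exposed (an assumption, since the article gives no rate), power would be about 90–91% or 81–83%, depending on whether the control variance is allowed to rise with the mean.
- *The plan must add an analysis by exposure.* Self-reported exposure after randomisation is open to bias when used for adjustment, and the contradiction can be corrected without it.

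**Conclusion.** The point holds as a contradiction in an operative data-collection rule. The question in the third safeguard of item (vi) conflicts with that paragraph's own account of contamination and with the allocation of materials in items (i), (iv) and (v). It is the article's only stated measure of cross-arm exposure.

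It is probably a slip. If it is fielded as written, the recorded number would not measure contamination and could reflect receipt of the controls' own MOH leaflet. The primary comparison is unaffected. The loss is confined to interpreting a small or null difference, and no numerical size can be put on it from the documents.

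The conclusion assumes that the questionnaire follows the article's wording. If the form already asks about the intervention leaflet, only the text needs correcting. The point is worth acting on because an error of this kind can pass unnoticed into a translated form, and after follow-up the information could be recovered only by going back to the participants.

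**What to change.** 1. In the third safeguard of item (vi), change the word control, where it says whose materials are meant, to intervention.
2. Check the questionnaire item, including any translated version. It should name or show the IEC leaflet so that participants do not confuse it with the MOH brochure.
3. Report the number of control participants who had access to the intervention leaflet, with the number asked as the denominator.

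The cost is one word in the protocol, a check of one questionnaire item and one line in the results. The sample size, the primary analysis and the visit schedule do not change.

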### Community tracing

In the event that a participant cannot be accessed for the second interview after the baseline one, then, we will ask the VHT to visit the physical location and find out the reason for non-response. The VHT will be provided with a Log to record this kind of information which could be loss of a phone and change in phone number of withdrawal from the study among other reasons. If the participant cannot be contacted on phone and physically (may have moved house), then we will consider this a loss to follow-up.

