### Statistical analysis

Objective 1: We will report frequencies and percentages of the study outcomes and their 95% confidence intervals. We will use regression analyses to determine associations between the primary outcome (MHL) and the factors that may be associated with it (demographics, CMD).

Objective 2: An intention-to-treat analysis will be conducted to compare the groups at baseline and within 4 weeks to assess the effects of the intervention on MHL. We will use a Student t test to examine this difference. The dependent variable (MHL) will be calculated as a continuous variable. Independent variables including presence of PD, MDD, GAD, PTSD, or SUD will be presented as continuous and categorical variables. Baseline characteristics of the intervention and control arms will be compared at the 5% level to assess if successful randomization was achieved. Data on potential confounders and effect modifiers, including variables that fail to achieve successful randomization (e.g., socio-demographic parameters) shall be used to control for confounding and effect modification. Between-subject analysis at week 4 will be used to assess the direct effect of the intervention by determining if there is a significant difference between the mean MHL scores in the intervention and control arms. Within-subject analysis will be performed among participants in the intervention arm by applying the Generalized Estimating Equations method on repeated measures data.

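### The primary comparison is called intention-to-treat, but the named t test makes it an available-case comparison, and loss to follow-up is worded in two unaligned ways

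*Protocol article*

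**What the plan says.** **Analysis.** Under Statistical analysis, Objective 2, the article states: "An intention-to-treat analysis will be conducted to compare the groups at baseline and within 4 weeks". The test follows: "We will use a Student t test to examine this difference". The between-arm contrast is described once more: "Between-subject analysis at week 4 will be used to assess the direct effect of the intervention". Generalized estimating equations on the repeated measures are named in the same paragraph, but only for a within-subject analysis of the intervention arm. The Abstract also uses the intention-to-treat label. Under Study outcomes, the primary outcome is the mean change in mental health literacy between arms.

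**Follow-up window.** Study procedure (vii) sets the target: "The time duration between baseline and follow-up is a week". It then extends it: "we will give an allowance of up to 4 weeks within which to conduct the follow-up interviews". It closes with: "should the participant not be available within the said 4 weeks, then we will consider them as lost to follow-up".

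**Tracing.** For a participant who cannot be accessed for the second interview, Community tracing says: "we will ask the VHT to visit the physical location and find out the reason for non-response". The village health team (VHT) member records the reason in a log. The section ends: "If the participant cannot be contacted on phone and physically (may have moved house), then we will consider this a loss to follow-up". It gives no time limit, and neither section refers to the other.

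**The concern.** A t test on follow-up MAKS, or on change in MAKS, needs a follow-up score from each person it includes. Anyone with a baseline score only falls out of the primary comparison. The label promises a comparison of everyone in the villages as allocated; the stated method gives a comparison of those who were re-interviewed. If the people not re-interviewed differ from the rest, and differ more in one arm than in the other, the estimated effect is biased and the label hides it.

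The two wordings of loss bear on this because they govern how long attempts to obtain a score go on. The trial is open-label, and the VHT members who do the tracing also distribute each arm's materials. Uneven tracing effort between arms is therefore possible, although nothing in the article shows that it will occur.

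**Working it through.** **1. The plan's own figure.** Inputs from Sample size and statistical considerations: mean 14.14, SD 2.19, effect 50%, 35 participants per village, coefficient of variation k = 0.25, power 80%, 95% confidence. I read the effect as a rise from 14.14 to 14.14 × 1.5 = 21.21, a difference of 7.07, and take a two-sided 5% level. The usual cluster-trial formula for means is

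c = 1 + (1.960 + 0.842)² × [2·SD²/m + k²(μ0² + μ1²)] / (μ1 − μ0)²

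- 2 × 2.19² / 35 = 0.274
- 0.25² × (14.14² + 21.21²) = 40.61
- 7.07² = 49.98
- c = 1 + 7.849 × 40.89 / 49.98 = 7.42, rounded up to 8 per arm

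This agrees with the article's figure of about 8.

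**2. Does loss cost power?** With 20% loss, m = 35 × 0.8 = 28 and c = 7.43, still 8. With 12 villages per arm, power is 95.6% both without loss and with 20% loss. Between-village variation dominates the formula, so on the plan's inputs loss matters for bias and not for power.

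**3. Possible bias.** If a share L of an arm is lost, the arm's available-case mean differs from its full mean by

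shift = L × (mean of retained − mean of lost)

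The documents give neither L nor the difference. Assuming a difference of 1 SD (2.19) in one arm only:

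| Loss in that arm | Shift (MAKS points) | Share of planned 7.07 |
|---|---|---|
| 5% | 0.05 × 2.19 = 0.11 | 1.5% |
| 10% | 0.10 × 2.19 = 0.22 | 3.1% |
| 20% | 0.20 × 2.19 = 0.44 | 6.2% |

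If both arms had the same loss and the same difference, the shifts would cancel. The planned difference is large (7.07 / 2.19 = 3.2 SD). If the true effect were 0.5 SD, or 1.1 points (also an assumption), the shifts at 10% and 20% loss would be 20% and 40% of it.

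**4. The two loss wordings compared.**

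- *Not reached by phone or visit in week 2.* Community tracing allows this person to be called lost at once; Study procedure (vii) still allows interviews until week 4. If attempts stop, a score that could have been obtained is not.
- *Reachable by phone but not interviewed by week 4.* Lost under Study procedure (vii); not covered by the Community tracing wording. Only the label differs, because the article provides for no interview after 4 weeks.

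Only the first case changes who can enter the t test.

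**The case against.** **The two sections can be read together.** Trace first, then close at 4 weeks; Statistical analysis uses the same 4-week limit. This stands: there is no flat contradiction, and Community tracing gives a condition for loss without saying that it is the only one. What remains is that the article does not state the sequence, so early close-out is left open.

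**Missing-data handling belongs in the full protocol or analysis plan.** This also stands, and the lack of a missing-data rule is not the point. The article never says that lost participants are dropped; that follows from the test it names. The objection to that test for a comparison labelled intention-to-treat holds whatever another document adds. One can say that intention-to-treat here means only analysis by the village's allocated arm. That is compatible with the text, but it leaves the comparison restricted to those with a follow-up score.

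**Stronger readings that a reader might infer.**

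- *That membership of the analysis depends on which loss rule a site applies.* The article describes no local choice of rule, and the same research assistants do both interviews. Entry to the t test depends on having a score, not on the loss label.
- *That withdrawal cannot be told apart from being unreachable.* The tracing log lists withdrawal among the reasons to be recorded.
- *That 42 of 420 per arm would be dropped and the effect overstated by 11%, or by 25% at 20% loss.* The 10% is an allowance for incomplete interviews in the baseline prevalence sample size, not a follow-up loss rate. The ratios 1/0.90 and 1/0.80 further need every lost intervention participant to gain nothing, with no change or loss effect among controls.

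**Conclusion.** The point holds in a limited form. The stated primary test yields an available-case between-arm comparison under an intention-to-treat name, and the only repeated-measures method named does not compare the arms. The differing loss wordings are secondary: they can be reconciled, but as written they allow attempts to end early.

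The size cannot be fixed from the documents. With 5% to 20% loss in one arm and the lost differing by 1 SD, the arm mean shifts by about 0.11 to 0.44 MAKS points. That is small beside the planned 7.07 points, but would matter if the real effect were much smaller. Both the loss rate and the 1 SD difference are assumptions, and the direction of the shift is unknown. Power is not the issue.

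**What to change.** 1. In Statistical analysis, replace the t test with a mixed model of baseline and follow-up MAKS in both arms, with a village random effect and allowance for the correlation between a person's two scores. Include every participant with a baseline MAKS, in the arm to which the village was allocated.
2. Report loss to follow-up by arm.
3. Add a sensitivity analysis that sets each lost participant to no change from baseline. The mixed model relies on data missing at random and alone does not correct bias when loss depends on the unseen score.
4. In Community tracing, state that tracing continues to the 4-week cut-off in Study procedure (vii).

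The cost is modest extra analysis work and a few sentences of protocol text. No additional participants or visits beyond the existing 4-week allowance are needed.
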